### Health economic measures

A cost-utility analysis will be performed to compare costs and quality-adjusted life years (QALYs) associated with the intervention and the standard of care over a 24-month period. The analysis will be conducted from the perspective of Canada’s publicly funded healthcare system, and resource use will be measured via a retrospective chart review. Only Canadian sites will be included in the economic analysis because of the important differences in healthcare systems between countries, with general consensus among health economists that power issues do not apply to these types of analyses. We will include the intervention costs (i.e., PAO and arthroscopy procedure) and health utilization-related costs. Health utility scores will be derived from the PROMIS score for each trial participant using a validated algorithm [62]. QALYs will be estimated using the total area under the curve method [63]. The statistical analysis will be conducted in accordance with current guidelines for clinical and cost-effectiveness analysis alongside RCTs [64]. The incremental cost and QALY will be estimated using generalized estimating equations that explicitly allows for the modeling of normal and non-normal distributional forms of repeated measure data. The cost per QALY gained will be obtained through the difference in average costs of the two treatment options divided by the difference in average QALYs as denoted by the coefficient of the therapy indicator variables. Uncertainty in the analysis will be addressed by estimating 95% confidence intervals using a non-parametric bootstrapping method. As a secondary analysis, we will use a societal perspective and consider productivity loss as measured through the work productivity and activity impairment questionnaire (WPAI:SHP) (completed at 6, 12, and 24 months), which has been used in studying patients after elective orthopedic surgery [65] (Additional file 9).

### Sample size and power calculation

A total sample size of 126 subjects is planned. Calculation of the required sample size is based on ensuring sufficient statistical power to detect a difference in the primary outcome measure (i.e., iHOT-33) at 12 months. The standard deviation of the iHOT-33 is approximately 16 in pre-arthritic patients [66–68]. The original iHOT-33 manuscript reported a minimal clinically important difference (MCID) of 6.1 in a general symptomatic hip population [66]. Since then, three other studies focusing on hip arthroscopy reported MCIDs varying from 10 to 12 [67–69] in time ranges varying from 6 to 12 months. Using a non-central *t* function with a conservative MCID of 10, an alpha level of 0.05, a power of 0.90, and a loss to follow-up of 15% provides a total sample size of 63 per group (total of 126).

For the T1ρ analysis, part of the subjects from each of the two subgroups will undergo quantitative hip cartilage MRI T1ρ-mapping. Our group has shown T1ρ to be a valid alternative to the gold standard (dGemric) for patients with symptomatic hip dysplasia (Additional file 1). Based on our hypothesis that patients undergoing in arthroscopy+PAO will conserve cartilage characteristics, whereas those with PAO only will demonstrate affected cartilage, the sample size for this study is calculated using a power analysis on T1ρ data from our longitudinal cartilage T1ρ study (two time points, mean follow-up time of 24.5 months) on corrective surgery for cam deformity in association with FAI [70]. Two years after surgery, T1ρ decreased significantly (*p* < 0.05) in the anterosuperior area of cartilage from 34.6 to 29.4 ms reaching control T1ρ values. By assuming a standard deviation of the mean T1ρ value of 5%, a power of 0.9, and alpha error of 0.05, we calculated that 21 subjects are needed for each of the two subgroups. Based on the follow-up loss rates from the former study (5 of 24; 20%) with this patient population, we will recruit a total of 26 patients per subgroup which will undergo the additional cartilage T1ρ-mapping protocol [57].

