#### MRI T1ρ cartilage mapping

The association between hip arthroscopy outcomes and cartilage quality is not well elucidated in the literature. The quality of the hip articular cartilage will be assessed by a non-invasive and validated MRI technique called T1ρ mapping that enables the evaluation of proteoglycan content [55, 56]. The cartilage will be segmented on co-registered anatomical MR images and quantitative cartilage T1ρ values will be measured in six regions over the cartilage [57]. The T1ρ relaxation time is sensitive to the cartilage proteoglycan content and increasing when the proteoglycan content is decreasing. We will compare the cartilage T1ρ relaxation times at the initial scan and at the follow-up scan (24 months after surgery) in the different regions to investigate changes in the cartilage macromolecule content after surgery. The significance of the differences in T1ρ will be tested using a paired t-test with a significance level of *p* < 0.05.

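### The 21 patients per arm for the T1ρ imaging subgroup do not follow from the stated inputs, which give about 4 per arm

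*Protocol article*

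**What the plan says.** The T1ρ paragraph of the protocol article, under Sample size and power calculation, takes its planning data from the team's own two-time-point study of surgery for cam deformity. In that study T1ρ fell significantly "in the anterosuperior area of cartilage from 34.6 to 29.4 ms reaching control T1ρ values". The next sentence begins "By assuming a standard deviation of the mean T1ρ value of 5%, a power of 0.9, and alpha error of 0.05" and ends "we calculated that 21 subjects are needed for each of the two subgroups". Allowing for about 20% loss to follow-up (5 of 24 in the earlier study), the plan is that "we will recruit a total of 26 patients per subgroup".

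The hypothesis given for the calculation is a contrast between arms: "patients undergoing in arthroscopy+PAO will conserve cartilage characteristics, whereas those with PAO only will demonstrate affected cartilage". The paragraph labels no figure as the target difference, and it does not give the sidedness of the test, a pre/post correlation or a formula. The section MRI T1ρ cartilage mapping says: "The significance of the differences in T1ρ will be tested using a paired t-test". The section Analyses and frequency of analyses names a repeated measures ANOVA for the pre-operative and follow-up scans.

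**The concern.** An SD of 5% is very small beside a fall of 5.2 ms, which is 15% of the starting value. The standardised effect is above 3, and an effect that large needs only a handful of patients per arm. Either 21 was computed from other inputs, or one of the printed inputs is wrong.

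What is at stake is how the imaging result will be read. Cartilage health is part of the primary objective under Principal research questions, although T1ρ is listed as a secondary outcome and measured in 52 of the 126 patients. A reader who accepts a 5% SD will take a null result from 21 patients per arm as strong evidence against even small differences. If the SD was really 5 ms, the same null result would say little about anything below about 5 ms.

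**Working it through.** **Inputs, all from Sample size and power calculation.** Difference Δ = 34.6 − 29.4 = 5.2 ms, the only T1ρ difference given. SD = 5% of the mean: 0.05 × 34.6 = 1.73 ms, 0.05 × 32.0 (midpoint) = 1.60 ms, or 0.05 × 29.4 = 1.47 ms. Power 0.90, alpha 0.05, two equal arms. Two-sided testing is my assumption.

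**Attempt to reproduce 21.** For two arms of size n, power comes from the non-central t with 2n − 2 degrees of freedom and non-centrality (Δ/SD)·√(n/2). The protocol names a non-central t function for its primary calculation.

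| SD (ms) | Δ/SD | Power, n = 3 | Power, n = 4 | Required n per arm |
|---|---|---|---|---|
| 1.73 | 3.01 | 0.78 | 0.94 | 4 |
| 1.60 | 3.25 | 0.84 | 0.97 | 4 |
| 1.47 | 3.54 | 0.89 | 0.98 | 4 |

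At n = 21 the power on these inputs exceeds 0.999.

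**Variants, keeping SD = 5% and Δ = 5.2 ms.**
- Normal approximation, 2(1.960 + 1.282)²(SD/Δ)²: 2 to 3 per arm.
- One-sided t: 3 per arm.
- Paired t: 4 patients, or 5 if the SD of the change is SD·√2.
- Two-arm comparison of change scores, SD·√2: 5 to 6 per arm.
- Bonferroni over the six cartilage regions: 5 to 6 per arm, or 7 to 9 for change scores.

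None comes near 21.

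**What does give 21.**
1. *SD = 5 ms, Δ = 5.2 ms.* Δ/SD = 1.04. The non-central t gives power 0.893 at n = 20 and 0.908 at n = 21, so exactly 21 per arm (the normal approximation gives 20). With Δ = 5.2 ms, 21 results only for SDs of about 4.94 to 5.07 ms. An SD of 5 ms is 14% of 34.6, 16% of 32.0 or 17% of 29.4.
2. *SD = 5%, smaller target.* With 21 per arm, 90% power corresponds to Δ = 1.025 SD: 1.025 × 1.73 = 1.8 ms, or 1.5 ms for SD = 1.47 ms. A nearby case is a 5% difference with a 5% SD (Δ/SD = 1), which gives 2 × (1.960 + 1.282)² = 21.0 before rounding by the normal formula and 23 by the t-test. No such target is stated.
3. *5% read as a standard error.* With 19 completers and the midpoint mean, SD = 1.60 × √19 = 7.0 ms, and a one-group paired t-test needs 21. This takes several unstated choices and does not test the between-arm hypothesis, for which the same SD needs 39 per arm.

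**Detectable between-arm difference, 21 per arm, 90% power, two-sample t.** 1.025 × 5 = 5.1 ms if the SD is 5 ms; 1.025 × 1.73 = 1.8 ms if it is 5% of 34.6. The ratio is 5/1.73 = 2.9.

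**Loss to follow-up.** 21/0.80 = 26.25, so the stated 26 is consistent with 21 to within rounding.

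**The case against.** The strongest defence is that 5.2 ms is never called the target. The paragraph reports it as the result of the earlier study and then lists SD, power and alpha. If the intended target was about 1.8 ms, a 5% SD and 21 per arm agree, and the fault is an omitted difference rather than a wrong SD. This stands, and it is why the cause cannot be fixed from the document. It does not rescue the text, because the only difference offered is 5.2 ms and that does not lead to 21.

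A reader might infer that 21 can only have come from an SD of 5 ms, and that the imaging subgroup can therefore detect nothing smaller than a full return to control values. The exact match at 5 ms makes a unit slip plausible, but nothing in the document confirms it. On the inputs as printed, the subgroup is larger than needed, so low sensitivity is not established.

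A reader might also fault the planning effect because it is a within-patient fall after cam surgery, whereas the hypothesis is one arm preserved and the other worsening. The protocol discloses that source openly. Planning from the nearest available data is a judgement, not an arithmetic error, and adds no weight here.

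**Conclusion.** The concern holds as a failure of reproduction. On the stated inputs about 4 patients per arm suffice, and no more than 9 under the variants above, against the stated 21. This assumes Δ = 5.2 ms, which the quoted means imply but the text does not label, and two-sided alpha 0.05; a one-sided test only lowers the number. Which input is wrong or missing remains open: an SD of 5 ms and an unstated target near 1.8 ms both explain 21. The sensitivity claimed for the subgroup is uncertain by a factor of 2.9, which is simply the ratio of the two candidate SDs.

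The finding covers the imaging subgroup only. The iHOT-33 calculation for 126 patients is separate and unaffected. The point should be fixed but does not threaten the trial: the justification is wrong as written, and underpowering is not shown.

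**What to change.** Restate the T1ρ calculation with four items:
- the SD in ms, with its source, and whether it is the SD of a single scan or of the change;
- the target between-arm difference in ms;
- the test used for the calculation, aligned with the analysis that will address the between-arm hypothesis, since the two tests now named are described for pre-operative against follow-up values;
- the sidedness of alpha.

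Together these must reproduce 21 evaluable (26 recruited) per arm. Add the difference detectable at 90% power with 21 per arm: for a two-sample comparison, about 5.1 ms if the SD is 5 ms and about 1.8 ms if it is 1.73 ms. Leave the enrolled number as it is.

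The cost is one or two sentences and a look back at the original calculation. If the SD proves to be 5 ms, the protocol will have to state a lower sensitivity than its 5% implies.

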### Analyses and frequency of analyses

The analysis will be conducted on an intention-to-treat basis. Statistical analyses will be performed blinded to treatment allocation. A level of significance of 0.05 will be used for all analyses. The underlying assumptions of all statistical procedures will be evaluated, and data transformation will be considered. Using descriptive statistics, baseline patient characteristic differences between the study groups will be assessed (age, sex, outcomes) and differences will be controlled for in the statistical analyses. Repeated measures mixed models and general linear mixed models will be used for handling continuous and dichotomous outcomes respectively. Sex will be specifically assessed as an effect modifier in the analyses. Multiple imputation will be considered as a sensitivity analysis.

For cartilage health, the biochemical content of the cartilage will be evaluated using MRI T1ρ mapping. The scan will be performed pre- and 2 years after surgery using a 3D turbo spin echo acquisition method with T1ρ preparation (CUBE QUANT) and the following parameters: TR = 1350 ms, TEeff = 40 ms, FOV = 25.6 × 25.6 cm^2^, in-plane resolution = 0.5 × 0.5 mm^2^, slice thickness = 3 mm, number of slices = 32 slices, no slice gap (3D sequence), B1 = 500 Hz, spin-lock times = 1, 15, 30, 45 ms, and scan time = 18 min [56, 71] (Additional file 1, Figure 3). For post-pressing, T1ρ-weighted datasets will be co-registered to the proton density-weighted turbo spin echo images and analyses described in our previous publications [57, 70]. The hip cartilage will be divided in six regions of interest (ROIs): anterior lateral, anterior middle, anterior medial, posterior lateral, posterior middle, and posterior lateral for regional proteoglycan assessment [57]. T1ρ values from the different cartilage regions will be compared and evaluated for significant differences between the pre-operative and the follow-up scan using repeated measures analysis of variance (ANOVA).

In addition to the final analysis, an interim analysis will be performed after 2.5 years to determine if the study must be terminated. This will be based on the following results: serious adverse events significantly higher in the experimental group, greater than expected beneficial effects, improbable statistically significant difference by the end of the study, and participant recruitment is severely lagging and unlikely to achieve the target.

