### Randomization

Randomization will be carried out in blocks randomly varying between 2 and 4 to ensure equal numbers in both treatment arms (i.e., “PAO” and “Scope-PAO”). Randomization will be stratified by recruiting site to allow for even distribution of intervention covariates and patient characteristics across each site and by sex to ensure adequate distribution of this variable for the analyses. Patients will be randomized just after enrolment, because MRI sensitivity is inadequate to identify intraarticular pathologies [28]. This will allow the surgeon’s office and treating institution to appropriately plan for the required surgical intervention, necessary equipment, operating room time, etc. Patients will be randomized through an on-line computer randomization program that will be accessible by designated research staff from all participating sites.

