### Primary outcome measure

#### iHOT-33

Disease-specific patient-reported quality of life will be the primary outcome used for comparison between the two treatment groups as measured by the International Hip Outcome Tool (iHOT-33). The iHOT-33 is a reliable, validated, self-administered quality of life assessment tool for young, active patients with hip symptoms [50]. The iHOT-33 is a core measure for this patient population [51, 52]. Patients will complete this questionnaire pre-operatively and at the following time intervals post-operatively: 6 months, 12 months (primary time point), and 24 months (Additional file 5). The value of the iHOT-33 at each time point will be used for analysis. Data will be aggregated such that the mean scores in each treatment group will be compared at each time point. In addition, the proportion of patients in each treatment group that have an increase in their score greater the minimum clinically important difference (MCID) of the score will be compared.

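### Covariates are chosen by observed baseline differences with no threshold, so adjustment for baseline iHOT-33 and site is not guaranteed and available precision may be lost

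*Protocol article*

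**What the plan says.** Under Analyses and frequency of analyses, the protocol article states how covariates are chosen: "baseline patient characteristic differences between the study groups will be assessed (age, sex, outcomes) and differences will be controlled for in the statistical analyses". The comparison is made with descriptive statistics. No significance level, standardised difference or other cut-off is named.

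The same paragraph gives the model class, "Repeated measures mixed models and general linear mixed models will be used for handling continuous and dichotomous outcomes respectively", and adds that "Sex will be specifically assessed as an effect modifier in the analyses".

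Under iHOT-33, the score is collected before surgery and at 6, 12 (primary) and 24 months, and "The value of the iHOT-33 at each time point will be used for analysis".

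Under Randomization, "Randomization will be stratified by recruiting site", and also "by sex to ensure adequate distribution of this variable for the analyses". Site does not appear among the characteristics to be compared at baseline. Nothing in the article commits to baseline iHOT-33 or site as a model term whatever the observed imbalance.

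**The concern.** In a randomised trial, baseline differences between arms arise by chance. The reason to adjust for a variable is that it predicts the outcome, not that it happens to differ. The stated rule uses the second criterion, with three consequences.

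- **Baseline iHOT-33 enters only if the arms look different.** It is likely to be among the stronger predictors of the 12-month score, and it is measured in every patient.
- **The rule works against the design.** Stratification keeps site and sex balanced, so a rule triggered by imbalance would seldom bring them in, and site is not on the list at all. Leaving stratification factors out of the model tends to make standard errors larger than they need be.
- **The primary model is not fixed in advance.** With no threshold, two analysts could both follow the text and fit different primary models.

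What is at stake is precision already paid for, and a primary analysis that can be named before data are seen.

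**Working it through.** **Inputs from the sample size section:** difference 10, SD 16, alpha 0.05 (two-sided assumed, since sidedness is not stated), power 0.90, loss 15%, 63 per group.

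**Input not in the document:** the correlation ρ between baseline and 12-month iHOT-33. It is taken as 0.2 to 0.7.

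**Step 1. The plan's own figure.** n = 2(1.960 + 1.282)² × 16²/10² = 53.8, so 54 per arm. The non-central t gives 55 (power 0.901; 54 gives 0.896). Allowing for 15% loss, 54/0.85 gives 64 and 55/0.85 gives 65; 54 × 1.15 = 62.1 gives 63. The stated 63 is reproduced within two patients, with no covariate in the calculation. Expected completers are 63 × 0.85 = 53.6, about 54 per arm.

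**Step 2. What adjustment offers.** Adjusting for baseline reduces the residual SD to 16 × √(1 − ρ²). Unadjusted power at 54 per arm is 89.6%. Always adjusting gives 90.7, 92.1, 94.0, 96.0, 98.0 and 99.5% at ρ = 0.2, 0.3, 0.4, 0.5, 0.6 and 0.7.

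**Step 3. How often the rule would omit baseline iHOT-33.** The standardised baseline difference has standard error √(2/54) = 0.192. The chance that it exceeds 0.2 is about 0.30, and that it exceeds 0.1 about 0.60. Baseline is therefore left out in about 70% of trials with a 0.2 threshold and 40% with a 0.1 threshold. With entry at p<0.05 it is left out in 95%.

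**Step 4. Power lost by the rule.** Simulation used 40,000 trials per setting, 54 per arm and a single 12-month comparison. The loss is the power of always adjusting minus the power of adjusting only when the entry rule is met, in percentage points.

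| ρ | p<0.05 | p<0.10 | std. diff. >0.2 | std. diff. >0.1 |
|---|---|---|---|---|
| 0.2 | 0.7 | 0.7 | 0.5 | 0.3 |
| 0.3 | 2.0 | 1.8 | 1.3 | 0.6 |
| 0.4 | 3.6 | 3.2 | 2.1 | 1.0 |
| 0.5 | 5.6 | 5.0 | 3.0 | 1.3 |
| 0.6 | 7.2 | 6.2 | 3.9 | 1.8 |
| 0.7 | 8.3 | 7.0 | 4.0 | 1.6 |

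The loss is positive in every cell, from 0.3 to 8.3 points. In absolute terms, power under the rule stays between 89.6% and 97.9%.

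**Step 5. Type I error.** At ρ = 0.4 to 0.6 the rule's simulated type I error is 3.1 to 4.6% across the four thresholds. Over ρ = 0.2 to 0.7 it is 2.4 to 4.9%. It is at or below the nominal 5% throughout.

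Site and sex were not simulated. The point about them rests on the text and on the general direction of the effect.

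**The case against.** **The size is not a property of the protocol.** It depends on a correlation and an entry threshold that the article does not state. The baseline comparison is descriptive, so a p<0.05 entry rule is only one reading, and the costliest of those tried. With a 0.1 threshold, baseline iHOT-33 would be included in 60% of trials and the loss is at most 1.8 points. A reader might infer that the baseline score will usually be dropped, or that a fixed loss of several points follows. The text supports neither. This stands, so the loss is given only as a range.

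**The trial is not underpowered.** A reader might also infer that the 90% power is eroded or that the false-positive rate rises. The sample size assumed no adjustment, and the rule is conservative. This stands.

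**The mixed model may already use baseline.** The pre-operative score is one of the measurement times. If it is modelled as a time point with equal means across arms, most of the gain is recovered. The simulation compares one follow-up time and does not represent that model. This is fair, but the article does not say that the model takes this form.

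**Sex is not ignored.** It enters the effect-modifier analysis. It is also on the list of characteristics compared. Only site is clearly absent.

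**Model terms can be left to an analysis plan.** That is true of silence about site. It does not cover the covariate sentence, which states a positive rule. An analysis plan that fixed covariates in advance would contradict it, and one that followed it would inherit the weakness.

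**The analysts are blinded and the rule looks only at baseline data.** This limits any steering towards a result. It does not fix the model or make imbalance the right criterion.

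**Conclusion.** The point holds as a matter of efficiency and prespecification. The article selects covariates by descriptively observed differences between randomised arms, with no threshold. Adjustment for baseline iHOT-33 is therefore not guaranteed, site is not among the variables considered, and sex is otherwise committed only as an effect modifier.

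Against an analysis that always adjusts for baseline iHOT-33, the rule gives up about 0.3 to 8.3 points of power. That range assumes 54 completers per arm, a difference of 10, SD 16, ρ between 0.2 and 0.7, and the four entry thresholds shown. It would be smaller if the mixed model already used baseline as a constrained time point. Neither the validity of the primary test nor the planned 90% power is in question. The change is worth making because it costs nothing and settles the primary model.

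**What to change.** Replace the covariate sentence with wording such as:

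> The primary mixed model for iHOT-33 includes arm, visit, arm-by-visit interaction, baseline iHOT-33, sex and site. Baseline iHOT-33 enters either as a covariate or as a baseline time point with means constrained equal across arms [state which]. The primary contrast is the arm difference at 12 months. No covariate is selected from observed baseline differences; the baseline table is descriptive.

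Use the same structure for the four-square step test, the sit-to-stand test and PROMIS Global 10, each with its own baseline value. Keep the assessment of sex as an effect modifier as a separate, additional analysis.

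The cost is a wording change by amendment. Baseline scores, sex and site are already recorded for every patient, and no further patients or visits are needed.

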#### Adverse events

Adverse events will be systematically queried and documented prospectively for the first 90 days [58] using Sink et al.’s classification system that grades the complications based on required treatment and long-term morbidity [59] (Additional file 7). Any other unexpected adverse events that are reported by the study participants will also be recorded for the duration of the study. The type of adverse event will be narratively reported in any publications along with their severity using the classification of Sink et al. [58]. Reoperation rate will also be monitored at 12 and 24 months post-operatively in each group using standardized failure modes [60] (Additional file 7). Although a recent retrospective chart review has demonstrated that there were no differences in reoperation rates between PAO alone and PAO combined with arthroscopy at minimum 2-year follow-up [61], there are obvious limitations in regard to selection bias, a prospective randomized trial might show otherwise (see Figure 4 in Additional file 8 for the figure as per Spirit guidelines).

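### Dichotomous secondary outcomes are assigned a general linear (normal-error) mixed model; a binomial model should be named instead

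*Protocol article*

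**What the plan says.** In the protocol article, the section Analyses and frequency of analyses gives the only statement of method for binary outcomes: "Repeated measures mixed models and general linear mixed models will be used for handling continuous and dichotomous outcomes respectively". It names no distribution, link, covariance structure or robust variance. The same section adds "A level of significance of 0.05 will be used for all analyses" and "The underlying assumptions of all statistical procedures will be evaluated, and data transformation will be considered".

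Two dichotomous outcomes fall under this sentence. The section iHOT-33 sets up a between-group comparison of "the proportion of patients in each treatment group that have an increase in their score" beyond the MCID. The section Adverse events says "Reoperation rate will also be monitored at 12 and 24 months post-operatively in each group", but gives no expected rate and no test for it.

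**The concern.** A general linear mixed model treats the residuals as normal and, in its simplest form, gives them one variance at all visits. A 0/1 outcome has variance p(1 − p), which moves with the proportion. Cumulative reoperation can only rise from 12 to 24 months. While it stays below 50%, its variance rises too, so a shared variance is too small at 24 months and too large at 12. The 24-month interval would then be too narrow and the 12-month interval too wide. A linear model can also return fitted proportions outside 0 to 1 when events are rare.

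What is at stake is the calibration of two secondary comparisons. The Adverse events section itself suggests that a randomised trial might contradict an earlier chart review on reoperation, so that comparison is likely to be read closely.

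**Working it through.** **Inputs.** From the article: SD 16, difference 10, alpha 0.05 (two-sided assumed), power 0.90, loss 15%, 63 per group, 1:1 allocation. Assumed, because the article gives none: all reoperation and MCID response rates.

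**Number per arm.** By the normal approximation, n = 2(1.960 + 1.282)² × 16²/10² = 53.8, so 54 per group. The planned 63 follows from 54 × 1.15 = 62.1. (Dividing by 0.85 gives 64, and a noncentral t calculation starts from 55; both are close to 63.) After 15% loss, 63 × 0.85 = 53.6, so 54 evaluable per arm are used below.

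**Case A: a linear model in which 24 months has its own variance** (a single time point, or an unstructured covariance). With no true difference and equal arms, both arms have the same variance p(1 − p), so the equal-variance assumption between arms is met. Exact binomial enumeration, 54 per arm:

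| 24-month rate | 3% | 5% | 10% | 15% | 20% |
|---|---|---|---|---|---|
| Type I error | 0.031 | 0.045 | 0.050 | 0.049 | 0.051 |

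There is no inflation.

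**Case B: one variance shared by the 12- and 24-month visits.** With v = p(1 − p) at each visit and v̄ the mean of the two, the large-sample error at 24 months is 2[1 − Φ(1.96 √(v̄/v24))]. For 5% rising to 10%: v12 = 0.0475, v24 = 0.0900, v̄ = 0.06875; √(0.06875/0.0900) = 0.874; 1.96 × 0.874 = 1.713; error 0.087. Simulation with no true difference, 54 per arm:

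| Assumed 12 → 24-month rate | Error at 24 months | Error at 12 months |
|---|---|---|
| 8 → 10% | 0.062 | 0.034 |
| 10 → 15% | 0.070 | 0.030 |
| 10 → 20% | 0.083 | 0.019 |
| 5 → 10% | 0.087 | 0.013 |
| 3 → 8% | 0.102 | 0.004 |
| 5 → 15% | 0.104 | 0.005 |
| 2 → 10% | 0.126 | below 0.001 |

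The range at 24 months is about 0.06 to 0.13. With 63 per arm the results are nearly the same (5 → 10%: 0.087; 5 → 15%: 0.106). The large-sample ceiling for two visits, as the 12-month rate tends to 0, is 2[1 − Φ(1.96/√2)] = 0.166. At 12 months the error is about 0.004 to 0.035 when at least 3% have been reoperated by then. It is lower still at 2%, where a linear model with its own variance is already conservative (0.016).

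**MCID response.** Take assumed response of 60%, 70% and 75% at 6, 12 and 24 months. The variances are 0.2400, 0.2100 and 0.1875, with mean 0.2125. The standard error used at 12 months is √(0.2125/0.2100) = 1.006 times the correct one. Across the response rates tried, the 12-month discrepancy was about −3% to +5%. At 6 and 24 months it can be larger if response climbs steeply at high levels: for 70%, 80% and 85%, the errors at the three visits are 0.082, 0.046 and 0.025.

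**Does a logit model alone restore 0.05?** Exact enumeration at 24 months, 54 to 63 per arm:

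| Rate | Wald | Likelihood ratio |
|---|---|---|
| 5% | 0.003–0.005 | 0.080–0.085 |
| 10% | 0.024–0.031 | 0.055–0.060 |
| 20% | 0.045–0.048 | 0.054–0.055 |

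Not when events are rare.

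**The case against.** The best defence is that this is a slip for *generalized*. The sentence separates the binary model from the continuous one, which would be odd if both had normal errors. The Health economic measures section names generalized estimating equations for non-normal data, so the team knows the distinction. Link and covariance structure are also details that an article may leave to the analysis plan. Much of this stands, and it is why the point is minor. It does not remove the point, because the article does state a model class, it is the wrong one, and no other section names a binary-data method. The promise to check assumptions and consider transformation does not help: no transformation makes a 0/1 variable normal.

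A reader might infer that the wording about doubles the false-positive rate for 24-month reoperation. The document does not support that. Doubling needs the two visits to be fitted jointly, one variance forced across them, and reoperations that at least double between 12 and 24 months. The article states none of these, and Case A shows no inflation.

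Nor does the article call reoperation its main safety comparison; it says that it will be monitored and names no test. The outcome explicitly to be compared is MCID response, which is little affected at 12 months, the primary time point.

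**Conclusion.** The named model is wrong for dichotomous outcomes as written, and the text should be corrected. The consequence is limited to secondary outcomes and depends on how the model would be fitted. With a variance shared across visits, the 24-month reoperation error is about 0.06 to 0.13 and the 12-month comparison is conservative, under assumed rates. With a separate variance per visit, the 24-month error stays at or below about 0.05. The primary comparison of mean iHOT-33 is unaffected. Severity: minor. Confidence is high on the wording. The size cannot be narrowed, because the article gives neither reoperation rates nor a covariance structure.

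**What to change.** In Analyses and frequency of analyses, replace the general linear mixed model for dichotomous outcomes with a generalized linear mixed model (binomial distribution, logit link). For MCID response, report a model-standardised risk difference with its 95% interval.

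For reoperation, where events may be few, state one of two approaches:

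- a comparison of proportions at 12 and at 24 months by an exact or penalised-likelihood method; or
- cumulative incidence by arm, with lost patients censored at last contact and the difference and interval given at both times.

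The second uses the reoperation-free time of the roughly 15% expected to be lost. It is a reasonable option rather than a correction of an error.

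The cost is a sentence or two and a little programming. The small downside is that a logit mixed model may not converge with very few events, and its Wald and likelihood-ratio tests are then miscalibrated, so the fallback should be named in advance.
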